#### Aim 2: To Compare Effects of an Inpatient PHR Engagement Intervention to a Virtual Cohort.

We will compare PHR engagement of our study participants to a virtual cohort of patients who were hospitalized but who were already regular users of their PHR. Patients in this virtual cohort will be identified through review of EMR data only and receive no intervention—they will serve as a benchmark for all participants (both intervention and control) in our study.

We hypothesize that those in the intervention group will be more likely than the control group to use their PHR while they are inpatients and after discharge and that patients in both the intervention and control groups will be more likely to use their PHR in these settings than the virtual cohort. In addition to testing these hypotheses, our project is designed to have significant impact on patient engagement with their care during hospitalization at our hospital. We will also add significant value to existing efforts by our health system to increase patient use of existing technologies: our system uses the PHR application called MyChart (Epic Systems Corp), a Web-based patient portal that allows patients to access to their PHR and perform health care tasks such as sending messages to providers, requesting appointments, viewing test results, and reviewing their medications. The overall objective of this research is to study the use of mobile platforms to improve transitions in care for older, hospitalized adults.

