Sources of data will include surveys that will be administered on the device, semistructured debrief interviews administered by assistants, and data on postdischarge access to the PHR from our EMR data repositories. All patients will answer basic questions about demographics, health literacy, and technology use in a preuse survey. The postuse survey will ask about satisfaction with the device to access their PHR and any technical issues. We have developed an interview tool for assistants to use to collect information about patient-reported problems with devices and ask open-ended questions about the overall experience using the tablet. During the debrief interview, the assistant will also ask the patient to demonstrate ability to access their PHR to view and verify their preadmission medications using their PHR medication list. Data about patient use of their PHR is compiled by our EMR in a searchable database (Clarity). We will query Clarity at 7 days to determine access and specific PHR tasks accomplished by all patients both during their hospital stay and for 7 days after discharge. We will also use the Clarity database to identify our virtual cohort of patients who were already engaged with their PHR (1 or more log-ins in the month prior to hospitalization) and were hospitalized during the same 12-month period of our study.

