Among older adults, 70% (15) owned a laptop, 58% (13) owned a desktop computer, 52% (11) owned a smartphone, and 42% (9) owned a tablet. Thus, mobile technologies pose an excellent venue to interact with this patient population. Trained research assistants spent at least 30 minutes with those patients who needed more assistance to become familiar with the tablets, but the majority needed 15 minutes or less, suggesting that most of them felt comfortable with using this technology. Indeed, our findings to date suggest that inpatients of all ages in both intervention and control groups require only minimal orientation from research assistants to use basic (eg, access Internet, check email) as well as more advanced functions (watch videos, complete tasks requiring more advanced navigation): 90% (41) of patients required 30 minutes or less for device orientation and 81% (36) required 15 minutes or less. Additionally, we found that after focused bedside teaching, most patients in our study were able to perform one or more key function in their PHR. These key functions included viewing their medication list (34, 76%), viewing scheduled appointments (38, 85%), viewing test results (38, 85%), and sending a secure message to their primary care provider (37, 82%). Additionally, 75% (34) reported they were satisfied or very satisfied with iPad tablet use for bedside access to their PHR to accomplish these tasks.

Because data is still being collected to compare patient groups within our study (intervention vs control), we compared PHR use among all participants (to date) in both groups to a virtual cohort of patients identified as regular users of their PHR prior to hospitalization. In most areas, both groups were similar, but our study group had significantly higher activity in medication list views (mean 2.12 views vs 1.07) and the virtual cohort had significantly higher use of the provider messaging function (mean 4.34 views vs 1.63) (Table 2).

**Table 2 table2:** Patient characteristics and PHR use in study participants compared to a virtual cohort of regular PHR users.

		Study group (n=45)	Virtual cohort (n=400)	*P* value
Inpatient characteristics				
	Hospital length of stay, days	5.79	4.51	.37
	Previous PHR experience, n (%)	22 (50)	400 (100)	<.01
PHR use during hospitalization				
	Logins per person, mean	2.74	2.99	.64
	Medication tab views, mean	2.12	1.07	<.01
	Test results tab views, mean	1.42	2.21	.28
	Appointments tab views, mean	0.69	1.34	.11

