	Provider messaging inbox views, mean	1.63	4.34	.04
PHR use after hospitalization (up to 7 days after discharge)				
	Logins per person, mean	4.04	3.87	.83
	Medication tab views, mean	2.93	1.46	<.01
	Test results tab views, mean	6.28	4.29	.37
	Appointments tab views, mean	2.72	2.01	.32
	Provider messaging inbox views, mean	3.91	6.11	.36

**Table 3 table3:** Adjusted PHR use during hospitalization by study group compared to virtual cohort group.

	Multivariable logistic regression^a^	
	OR for study group vs virtual cohort group mean	95% CI
Medication tab views	2.4	1.5-4.2
Test results tab views	1.1	0.7^-^1.8
Appointments tab views	0.71	0.5^-^1.1
Provider messaging inbox views	0.70	0.5^-^1.1

^a^Adjusted for age, gender, race/ethnicity, length of stay, and prior PHR experience.

In analyses adjusted for confounding, the higher rate of provider messaging seen in Table 3 disappeared with adjustment; however, the higher rate of medication list views persisted (odds ratio [OR] 2.4) (Table 3). In adjusted analyses of PHR use after discharge, there were no significant differences between the virtual cohort and the study group.

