## Discussion

### Principal Findings

Our preliminary findings demonstrate relatively high ownership and use of mobile devices among all patients (including those over age 50 years) and relatively low use of these devices for specific health care tasks that can be accomplished via patient PHRs. This gap between high device ownership/use and low engagement in PHR confirms a pattern seen in our previous work and suggests an opportunity to intervene in order to increase PHR engagement during and after hospitalization [19]. Regarding device use, national data from the Pew Research Center show that 55% of all adults own a smartphone and 43% own a tablet; our study shows higher rates, at 64% (29/45) for smartphones and 51% (23/45) for tablets [20]. Although this is only half of our planned total enrollment, this difference in level of tech-savviness may limit the generalizability of our results to less tech-savvy populations if these trends persist in our final sample.

Although we do not yet have data to report on differences between our intervention and control group, we are able to do some preliminary comparisons between both groups (all of whom received a tablet and assistance logging into their PHR) and a virtual cohort of patients who were regular PHR users but received neither tablets nor PHR assistance during hospitalization. Our findings to date show that patients in our study were more likely to use their PHR for viewing the medications during hospitalization. These findings suggest that providing tablets and even basic PHR assistance for patients in the hospital may be an intervention that can improve engagement among inpatients to resemble patterns seen in a group of patients who were already engaged in using their PHR before hospitalization. Once final data collection and analysis are complete for our study, we will explore differences between intervention and control patients and compare each group separately to the virtual cohort as a benchmark for PHR engagement.

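### The only adjusted Aim 2 model shown includes prior PHR experience, which every cohort member has by selection, so its odds ratio speaks essentially for participants who were already PHR users

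*Protocol article*

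**What the plan says.** - **Cohort selection** (Data Collection and Sources of Data). The comparator, found through the Clarity database, is a "virtual cohort of patients who were already engaged with their PHR (1 or more log-ins in the month prior to hospitalization". Prior use is thus a condition of entry.
- **Table 2** (Results). Prior PHR experience is 22 (50%) in the study group of 45 and 400 (100%) in the cohort of 400, P<.01.
- **Table 3** (Results; preliminary, inpatient use only). A multivariable logistic regression is footnoted "Adjusted for age, gender, race/ethnicity, length of stay, and prior PHR experience". The odds ratios for study group against cohort are 2.4 (1.5-4.2) for medication views, 1.1 (0.7-1.8) for test results, 0.71 (0.5-1.1) for appointments and 0.70 (0.5-1.1) for messaging. The text below it says that the messaging difference did not survive adjustment for confounding, while the medication difference did.
- **Aim 2**. The cohort is the benchmark for participants in both arms, and the hypothesis is that "patients in both the intervention and control groups will be more likely to use their PHR in these settings than the virtual cohort".
- **Principal Findings**. Tablets with basic help may "improve engagement among inpatients to resemble patterns seen in a group of patients who were already engaged in using their PHR before hospitalization". The final analysis is to compare each arm separately with the cohort.
- **Data Analysis**. No model or adjustment set is given for the cohort comparison, so the Table 3 footnote is the only one in the article.

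**The concern.** Adjustment for a covariate compares like with like across groups, and it needs both groups to have members at each level. Here the covariate is the comparator's selection rule, so the cohort has nobody at the no-experience level. Adjusting for it does not remove an imbalance between all participants and the cohort. It changes which participants are being compared.

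About half of the study group had no prior PHR experience. They are the people for whom a benchmark of already engaged users is most informative, and they contribute almost nothing to the adjusted odds ratio. A reader who takes Table 3 as the study group's result, or takes the lost messaging difference as confounding removed for everyone, would be misled. The same would happen in the final analysis if this adjustment set were kept.

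**Working it through.** **1. Reproduce the Table 2 row.** 22/45 = 48.9% and 22/44 = 50.0%, so the printed 50% suggests one missing value. Fisher's exact test of 22/45 against 400/400 gives P of about 2 × 10^-26, consistent with the printed P<.01.

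**2. What the group coefficient estimates.** Let G = 1 for the study group and E = 1 for prior experience, with logit(p) = a + bG + cE. Only three cells are filled:

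| Cell | n | logit(p) |
|---|---|---|
| Cohort, experienced | 400 | a + c |
| Study, experienced | 22 | a + b + c |
| Study, not experienced | 23 (22 if one value is missing) | a + b |

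Three parameters fit three cells exactly. Row 2 minus row 1 gives b = logit(study, experienced) - logit(cohort). Row 3 does not enter b; c absorbs it.

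**3. Illustration with assumed rates** (the article gives no patient-level rates). Take 13/22 for experienced participants and 160/400 for the cohort. With E in the model, OR = (13/9)/(160/240) = 2.17, and SE = sqrt(1/13 + 1/9 + 1/160 + 1/240) = 0.445.

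| Non-users with the outcome | OR with E | OR without E, all 45 |
|---|---|---|
| 2/23 (about 10%) | 2.17 | (15/30)/(160/240) = 0.75 |
| 7/23 (about 30%) | 2.17 | (20/25)/(160/240) = 1.20 |
| 12/23 (about 50%) | 2.17 | (25/20)/(160/240) = 1.88 |
| 16/23 (about 70%) | 2.17 | (29/16)/(160/240) = 2.72 |
| 21/23 (about 90%) | 2.17 | (34/11)/(160/240) = 4.64 |

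The all-participant odds ratio can lie on either side of the adjusted one. The table shows that the adjusted figure does not respond to non-users. It says nothing about where the trial's own value lies.

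**4. With other covariates.** Three further covariates were added in simulation, with 400 data sets per setting and a true experienced-stratum OR of 2.23. As the non-users' log-odds shifted by -1.5, 0 and +1.5, the median adjusted OR was 2.22 each time. Without E it was 0.83, 1.47 and 3.07. The match to a fit with the non-users deleted is then close but not exact: in a separate simulation with age, sex, race and length of stay, the two ORs differed by a median of 0.02 (95th percentile 0.11).

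**5. Extension to non-users.** Applying b to non-users assumes that the group effect is the same at both levels of E. Testing that needs the cohort/no-experience cell, which is empty by design.

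**6. Messaging.** Table 2 shows mean inpatient inbox views of 1.63 against 4.34 (P=.04); Table 3 shows OR 0.70 (0.5-1.1). The change could come from removing non-users, from the other covariates, or from moving from means to odds. The article does not allow these to be separated.

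**7. Printed precision.** SE = ln(upper/lower)/3.92. In a binary logistic model each patient contributes information of at most 1/4, so SE is at least sqrt(4/n1 + 4/n0).

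| Table 3 row | SE from CI | Largest SE that rounding allows |
|---|---|---|
| Medications | 0.263 | 0.274 |
| Test results | 0.241 | 0.267 |
| Appointments | 0.201 | 0.239 |
| Messaging | 0.201 | 0.239 |

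The minimum is sqrt(4/22 + 4/400) = 0.438 for 22 against 400, and sqrt(4/45 + 4/400) = 0.314 for 45 against 400. All four rows fall below both. Around 2.4, an interval resting on 22 participants would be at least 2.4 × exp(±1.96 × 0.438), about 1.0 to 5.7, against the printed 1.5 to 4.2.

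**The case against.** The best defence has five parts.

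- **Table 3 is preliminary, and no model is fixed for the final Aim 2 analysis.** This stands. A reader might infer that the planned analysis discards non-users and that Aim 2 cannot answer its own question. The article does not show that; the problem carries over only if the same adjustment is kept.
- **The whole-group comparison is reported.** Table 2 sets all 45 against the 400 without adjustment, and log-ins are close (2.74 against 2.99 in hospital, 4.04 against 3.87 after discharge). This also stands. The Conclusions' statement that enrolled patients use their PHR at similar rates can rest on Table 2, so it is not shown to depend on Table 3. The inference in Principal Findings is hedged, and it pools both arms.
- **Reversed odds ratios are not observed.** Correct. A reader might infer from the illustration that the true direction flips, but those values follow from assumed rates. In the article, medication views are higher in the study group both unadjusted (2.12 against 1.07) and adjusted (OR 2.4), and appointments and messaging keep their direction.
- **The identity is inexact, and the coding is unknown.** Correct in part. Other covariates make it approximate, and a graded experience term would not confine the odds ratio to the 22. Non-users would then be compared with the cohort only by extrapolation. Since the printed intervals fit no per-patient binary logistic model, what was fitted is uncertain.
- **Experienced participants against the cohort is a legitimate contrast.** Yes, and it is close to what Table 3 estimates. The defect is that it is labelled as the study group's result and that no non-user contrast stands beside it.

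None of this supports reading the adjusted odds ratio as an effect for all participants.

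**Conclusion.** The point holds in a limited form. With prior experience as a yes/no main effect, which is how Table 2 tabulates it, Table 3's group odds ratio is essentially the contrast of the 22 already experienced participants (49% of 45) with the 400. It should not be presented as the whole study group's effect, and the statement that the messaging difference went away after adjustment for confounding cannot be taken to cover non-users.

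The size and direction of any change in the trial's own odds ratios are unknown without patient-level data. Separately, the printed intervals are too narrow for a per-patient binary logistic model even with all 45 participants, so the outcome coding and the fitted model need checking.

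This concerns a secondary, non-randomized benchmark. The comparison of intervention with control is not affected.

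**What to change.** 1. In the final by-arm comparison with the cohort, drop prior PHR experience from the all-participant model and keep age, gender, race/ethnicity and length of stay.
2. Report two further contrasts by arm: participants who meet the cohort's own rule (1 or more log-ins in the month before admission, taken from Clarity) against the cohort, and participants who do not meet it against the cohort. Use that rule for both groups, because the article does not say how prior experience was defined for the study group.
3. Relabel the current Table 3 odds ratios as applying to experienced participants, and limit the messaging statement in the same way.
4. Base any statement that newly engaged patients resemble engaged users on the non-user contrast.
5. State the outcome coding, the coding of prior experience and the model behind Table 3, and recheck its intervals.

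**Cost.** Analysis code and wording; no new data collection beyond a Clarity query. Precision is the real price. With 100 enrolled, about 50 per arm and half of them prior users, each stratum has about 25 patients per arm. For a binary outcome against 400, SE is at least sqrt(4/25 + 4/400) = 0.41, so a 95% interval spans at least the odds ratio divided and multiplied by exp(1.96 × 0.412) = 2.2. These contrasts will be descriptive, and their intervals should be shown.

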## Discussion

### Principal Findings

Our preliminary findings demonstrate relatively high ownership and use of mobile devices among all patients (including those over age 50 years) and relatively low use of these devices for specific health care tasks that can be accomplished via patient PHRs. This gap between high device ownership/use and low engagement in PHR confirms a pattern seen in our previous work and suggests an opportunity to intervene in order to increase PHR engagement during and after hospitalization [19]. Regarding device use, national data from the Pew Research Center show that 55% of all adults own a smartphone and 43% own a tablet; our study shows higher rates, at 64% (29/45) for smartphones and 51% (23/45) for tablets [20]. Although this is only half of our planned total enrollment, this difference in level of tech-savviness may limit the generalizability of our results to less tech-savvy populations if these trends persist in our final sample.

Although we do not yet have data to report on differences between our intervention and control group, we are able to do some preliminary comparisons between both groups (all of whom received a tablet and assistance logging into their PHR) and a virtual cohort of patients who were regular PHR users but received neither tablets nor PHR assistance during hospitalization. Our findings to date show that patients in our study were more likely to use their PHR for viewing the medications during hospitalization. These findings suggest that providing tablets and even basic PHR assistance for patients in the hospital may be an intervention that can improve engagement among inpatients to resemble patterns seen in a group of patients who were already engaged in using their PHR before hospitalization. Once final data collection and analysis are complete for our study, we will explore differences between intervention and control patients and compare each group separately to the virtual cohort as a benchmark for PHR engagement.

### Strengths

While our results are preliminary, we believe this project has potential to be innovative in several ways. First, our study will be one of the first to explore a patient-centered mobile health approach to engage adult patients in hospital and postdischarge settings. Furthermore, by exploring patient experiences with mobile devices, our research will enable us to carry out future projects to engage hospitalized patients in a variety of tasks. For example, we would like to build on experience from the current project to use patient PHRs at bedside in the hospital for more advanced discharge planning in coordination with multidisciplinary team rounds. Finally, our focus on older adults is especially important as they represent a large portion of our health system’s inpatient population, they are at particularly high risk for poor outcomes of transition care, and they are the least likely to be familiar with their PHR or to use it meaningfully without targeted interventions.

### Limitations

Despite these strengths, our study has several limitations which will be important to contextualize our preliminary and final results. First, this is a relatively small study (planned enrollment of 100) which may limit our ability to detect small differences between the intervention and control groups. Second, there may be participation bias in our sample as our preliminary data suggest participants to date have been more tech-savvy than national data (ie, it may be that less tech-savvy patients are less inclined to agree to participate). Third, we did not include education or income in our survey instruments so we will not be able to determine to what extent these factors explain the tech-savviness of our participants, although we will be able to extract other traditional determinates of low technology use such as race/ethnicity and payer status (eg, Medicaid vs Medicare or private insurance) from our EMR for final analysis. Finally, we did not conduct postdischarge interviews so we do not know how patient perspectives on using their PHR might change over time; this is an important question for future studies. Future studies may also consider following patients for longer than 7 days after discharge (eg, 30 days), although we did not find any significant results at 7 days so stronger postdischarge reinforcement may be needed for future hospital-based interventions to create lasting impact.

### Conclusions

We have designed a protocol to examine whether the provision of tablet computers and varying levels of PHR assistance (log-in only for control, extensive guidance for intervention) can improve inpatient use of their PHR to engage in hospital care. Our preliminary results suggest that learning about the device is not a significant barrier and that all patients actively enrolled (intervention and control) use their PHR at rates similar to a passively enrolled virtual cohort of patients who were already engaged with their PHR. Our final results will examine whether the intervention patients are different than control patients in terms of inpatient and postdischarge use of their PHR or whether the mere provision of tablets and log-in assistance in the hospital might be enough to explain higher PHR engagement in these patients. Our results are designed to have real-world impact at our medical center and may have important applications for many other medical centers and health systems that are searching for effective implementation strategies to increase patient engagement with PHR systems already in use in their facilities.

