### Randomization and Intervention

To randomize patients into intervention and control groups, we used an Internet-based coin toss random number generator (Random.org). The research assistant performs this randomization process after patient screening and consent. If the result of the coin toss is heads, the patient is enrolled in the intervention arm; if the result is tails, the patient is enrolled in the control arm. Patients were enrolled Monday through Friday only, no weekends or holidays.

Our project will provide all study participants with tablets and access codes to MyChart while they are hospitalized. Intervention patients will also receive bedside training from study research assistants on key functions of MyChart including how to view medication lists (see Multimedia Appendix 1). Through our preliminary work, we have created a semistructured tutorial for this bedside training that assistants can administer to patients. While this tutorial allows for a basic level of content uniformity for all patients, it is flexible enough to allow assistants to speed up or slow down or otherwise tailor the depth of explanation to the needs of each individual patient (see Multimedia Appendix 2). This study was approved by the UCSF Institutional Review Board and registered at Clinicaltrials.gov [NCT02109601].

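### The only group without a tablet consists entirely of recent PHR users, so PHR-naive participants have no untreated counterpart for the question of what tablets plus log-in help achieve alone

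*Protocol article*

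**What the plan says.** Under Randomization and Intervention: "Our project will provide all study participants with tablets and access codes to MyChart while they are hospitalized". The arms differ in training only; the Conclusions describe "varying levels of PHR assistance (log-in only for control, extensive guidance for intervention").

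The comparison group without a tablet is described under Principal Findings as "a virtual cohort of patients who were regular PHR users but received neither tablets nor PHR assistance during hospitalization". Data Collection and Sources of Data gives its selection rule: patients "already engaged with their PHR (1 or more log-ins in the month prior to hospitalization"), hospitalized in the same 12 months. Aim 2 and Study Design call this cohort a benchmark.

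Three statements then lean on it:
- Aim 2 hypothesizes that "patients in both the intervention and control groups will be more likely to use their PHR in these settings than the virtual cohort".
- Principal Findings, in hedged terms, suggests from the preliminary data that tablets and basic help "may be an intervention that can improve engagement among inpatients to resemble patterns seen in a group of patients who were already engaged".
- The Conclusions say the final results will examine whether training makes a difference, or "whether the mere provision of tablets and log-in assistance in the hospital might be enough to explain higher PHR engagement in these patients".

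**The concern.** Saying that engagement is higher because of tablets and log-in help requires a reference: what similar inpatients do without them. The randomized comparison cannot supply it, because both arms have both components. The virtual cohort supplies it, at best, only for patients who already use the PHR.

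Two misreadings are at stake. If the arms do not differ, the Conclusions invite the reading that the shared component was sufficient, although a null contrast between two exposed groups says nothing about what they share. If participants resemble the cohort, that can be read as tablets having lifted them to that level, although resemblance is compatible with a large effect, a small one or none. Conversely, a result below the cohort could be read as no benefit when the comparator was chosen for the behaviour being measured. The Limitations section does not mention any of this.

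**Working it through.** **1. Who is exposed, and who has used the PHR before**

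| Group | Tablet and log-in help | Training | Prior PHR use |
|---|---|---|---|
| Intervention | yes | yes | mixed |
| Control | yes | no | mixed |
| Virtual cohort | no | no | 400 of 400 |

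Table 2 gives previous PHR experience as 22 (50%) of the 45 participants in both arms together; 22/45 = 48.9%. The cell for no tablet and no prior use is empty.

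**2. What adjustment can do.** Table 3 adjusts for prior PHR experience. Ignoring the other covariates, the model has three occupied cells (experienced participants, naive participants, experienced cohort) and three parameters (intercept, group, experience). The experience term is fixed by experienced versus naive participants, all of whom had tablets. The group term therefore reduces to experienced participants versus the cohort. Applying it to naive participants rests on the assumption that the tablet effect is the same in both kinds of patient, which no data here can check.

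**3. What similarity to the cohort tells us, using the article's own means.** In-hospital log-ins per person are 2.74 (participants) and 2.99 (cohort), P=.64. Assume that experienced participants without a tablet would have averaged 2.99, and let x be the unknown no-tablet mean of naive participants, from 0 to 2.99.

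- No-tablet mean of the participant mix = 0.5 × 2.99 + 0.5x.
- x = 0: 1.495, so the implied gain is 2.74 − 1.495 = +1.245 log-ins.
- x = 2.99: 2.99, so the implied gain is 2.74 − 2.99 = −0.25.

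The same two means fit anything from a gain of about 1.2 log-ins per person to a slight shortfall.

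**4. Direction and illustrative size for a proportion.** The article gives no proportions logging in without a tablet, so these rates are assumed: a = 50-70% for prior users and b = 5-30% for non-users.

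- Participants' no-tablet rate = 0.5a + 0.5b. The cohort's rate = a.
- Overstatement by the cohort = a − (0.5a + 0.5b) = 0.5(a − b).
- Smallest: 0.5 × (50 − 30) = 10 points.
- Largest: 0.5 × (70 − 5) = 32.5 points.

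A true gain of 20 points (also assumed) would appear as between 20 − 10 = +10 and 20 − 32.5 = −12.5 points. The direction needs only a > b; the size depends entirely on the assumed rates.

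**The case against.** The strongest reply is that the cohort is declared a benchmark, that Aim 1 is the randomized comparison, and that the sentence in the Conclusions is cautious and belongs to neither numbered aim. This is largely fair. The randomized comparison is untouched, and a high-use benchmark is legitimate. The sentence still announces a question for the final results that the comparator does not fit.

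A reader might infer more than the documents support:

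- *That the study can say nothing about tablets.* Not so. Experienced participants can be set against the cohort, and the bias in the overall comparison runs against the arms, so an excess is suggestive. Medication-list views already show one: 2.12 vs 1.07 in hospital, adjusted odds ratio 2.4 (95% CI 1.5-4.2). It is not clean evidence, because research assistants ask participants to open that list and Limitations describes participants as more tech-savvy than national data.
- *That half the participants were already regular users.* Table 2 records previous PHR experience, which is not shown to mean a log-in in the prior month.
- *That the article already claims a tablet effect.* Principal Findings says only that the findings suggest tablets may be such an intervention.
- *That the Aim 2 hypothesis is incoherent.* Asking participants to exceed a demanding benchmark is ambitious but possible.

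A stratified analysis may also exist in the full protocol or analysis plan, which is not shown. That would help for prior users. On the selection rule published here, it would not provide untreated non-users.

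**Conclusion.** The concern holds in limited form. The randomized contrast estimates the added effect of training. For tablets plus log-in help, the design offers a non-randomized comparison for prior users and none for PHR-naive participants, who are about half of those enrolled so far. Neither a null result between arms nor similarity to the cohort can show that tablets plus log-in help were enough to explain higher engagement. A null or lower result against the all-user cohort is not evidence of no tablet effect.

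This rests on the published selection rule, on the interim share of 22 in 45 staying roughly the same, and on prior users logging in more than non-users. The range of 10 to 32.5 points illustrates the possible bias under assumed rates; it does not measure the bias in this study. The gap is worth closing because it affects a stated conclusion and costs little to repair.

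**What to change.** - Keep the 400-patient cohort as a descriptive high-use benchmark.
- From Clarity, for the same units, the same 12 months and the criteria that can be checked in the EMR, draw a second no-tablet cohort without the prior-log-in requirement.
- Extract prior-month log-in status for participants as well, and compare within strata of that status or with weights on it. At minimum, compare only participants with a prior-month log-in against the existing cohort.
- Report this as non-randomized, with its caveats: participants are consenting and more tech-savvy volunteers, staff prompt medication-list views, and the survey covariates (health literacy, technology use) are absent in any EMR cohort.
- If no second cohort is drawn, limit the Conclusions to the added effect of training plus a descriptive benchmark, and list the missing untreated non-users under Limitations.
- Leave the Aim 2 hypothesis as it is, but state that the comparison with the all-user cohort is biased against the study arms. Recasting it as reaching the benchmark would need a margin, and would be a change made after interim results had been seen.

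Cost: one more EMR query, one extra variable for participants and one further comparison, with no additional enrolment. The new comparison remains observational.
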